#### **Secondary Aims**

**Aim 2:** To evaluate the effectiveness of BRIDGE's enhanced service integration approach on increasing retention in AIDS center, initiating ART, and increasing adherence to HIV treatment regimens and virologic suppression;

**Aim 3:** To assess how multi-level theory-driven factors (client, staff, agency, community, structural) influence the implementation and effectiveness of BRIDGE on Aim 1 and Aim 2 outcomes; and

**Aim 4:** To evaluate the implementation process and cost of BRIDGE including implications for cost-effectiveness, feasibility of expansion, and sustainability.

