### 2.4. STUDY ANALYSES

#### *Data analyses by study aim*

To test Aim 1 hypotheses, we will compare data on service linkage outcomes during post-intervention to service linkage outcomes during pre-intervention. Data for Aim 1 will be obtained from the AppSheet tracking system and process measures on ARTAS sessions.

For Aim 2, we will compare data on HIV testing in TPs, retention in HIV care, ART initiation, ART adherence, and viral suppression during post-intervention to these same data during pre-intervention. Data for Aim 2 will be obtained from the AppSheet tracking system and the AIDS Center Semi-Annual Report.

| Table 1: Measurement of Study's Outcome Variables           |                                                                                    |                                            |                                                 |
|-------------------------------------------------------------|------------------------------------------------------------------------------------|--------------------------------------------|-------------------------------------------------|
| Variable                                                    | Instrument/Measure                                                                 | Time point(s) a                 | Source                                          |
| Program Data                                         |                                                                                    |                                            |                                                 |
| PRIMARY OUTCOME: HIV-positive TP clients accessing HIV care | # and % of HIV-positive clients who visit HIV clinic $\geq 1$ time in past 90 days | Ongoing (checked quarterly)                | AppSheet tracking system                        |
| HIV-positive TP clients retained in HIV care                | # and % of HIV-positive clients who visit HIV clinic $\geq 3$ time in past 90 days | Ongoing (checked quarterly), semi-annually | AC semi-annual report, AppSheet tracking system |
| HIV testing at TP                                           | # and % of TP clients who have received an HIV test at TP                          | Ongoing (checked quarterly)                | AppSheet tracking system                        |

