### **PURPOSE OF REPORT**

The purpose of this report is to collect de-identified epidemiological and laboratory data on all HIV-positive people who inject drugs (PWID) served by an AIDS center in each of our four study sites.

The data provided in this report will be used to test the research question related to Study Aim 2, which seeks to evaluate the effectiveness of BRIDGE's enhanced service integration approach on increasing retention in HIV Care Clinic, initiating ART, and increasing adherence to HIV treatment regimens and virologic suppression. By comparing epidemiological and laboratory data between BRIDGE trust points and non-BRIDGE trust points, we will be able to evaluate the effects of implementing the BRIDGE intervention in a trust point.

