### **DATA SOURCE**

The data for the Semi-Annual Reports will be drawn from existing electronic medical records at each City AIDS Center. The Electronic HIV Case Management System (EHCMS) is a government-approved computer system for the collection, storage, transfer and analysis of epidemiological, laboratory and clinical data on all registered cases of HIV infection in Kazakhstan. Within this system, a file is created for each client who registers for treatment at the AIDS Center. All visits, tests, results and treatment information for each client are regularly entered by staff from the epidemiology and treatment department. . This system has been in place since 2011, and is used in all regions of the country. Each AIDS Center is responsible for assuring the quality of entered data through regular checks by specialists.

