## INDICATORS PROVIDED IN REPORT

Semi-annual reports shall contain following indicators:

- BRIDGE ID (as index)
- Age
- Sex
- Date when client's HIV-positive status was confirmed
- Name of the trust point where client has received services in the past 6 months
- Date registered as client of the AIDS Center
- Was the client given a CD4 test in the past 6 months?
  - Test system used for CD4
  - Results of CD4 test
- Was the client given a Viral Load test in the past 6 months?
  - Test system used for Viral Load
  - Results of Viral Load test
- Clinical Stage of Disease in the past 6 months
- Has the client begun ART?
  - Date when the client begun ART
  - Name of ART drugs (regimens)
- Changes in the client's ART regime in the past 6 months
- Changes in the specific ART medications in the past 6 months
- Testing for STIs at the AIDS Center in the past 6 months
  - STIs diagnosis in the past 6 months (if available)
  - Treatment for STIs (if available)
- Registration at the drug treatment clinic

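### ART adherence is a stated Aim 2 outcome, but the available text does not define it and the report assigned to it lists no variable that measures it

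*Combined protocol and SAP*

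**What the plan says.** Section 1.2 (Secondary Aims) lists adherence in Aim 2 beside two neighbouring outcomes: "initiating ART, and increasing adherence to HIV treatment regimens and virologic suppression". Section 2.4 repeats it in the pre/post comparison of "retention in HIV care, ART initiation, ART adherence, and viral suppression during post-intervention", and names two sources: "Data for Aim 2 will be obtained from the AppSheet tracking system and the AIDS Center Semi-Annual Report".

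Appendix B (Purpose of Report) gives the Semi-Annual Report the task of testing, among other things, "increasing adherence to HIV treatment regimens and virologic suppression". Its indicator section opens with "Semi-annual reports shall contain following indicators" and then itemises them. The ART entries are whether ART has begun, the start date, the drug names, "Changes in the client's ART regime in the past 6 months" and "Changes in the specific ART medications in the past 6 months".

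The report is drawn from the national electronic case system, in place since 2011. Appendix B (Data Source) says of that system: "All visits, tests, results and treatment information for each client are regularly entered by staff".

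Appendix A (Purpose of AppSheet Data Collection) describes AppSheet's part in Aim 2 as HIV testing at trust points and retention in HIV care. It does not mention adherence, ART initiation or viral suppression.

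**The concern.** The plan promises a test of adherence, but the source assigned to it appears to hold nothing that records whether treatment was collected or taken. If so, there are two ways it can end. Either the outcome goes unreported, or a substitute is chosen from what was collected, possibly after the data have been seen. The fields at hand answer other questions: whether treatment was started, what was prescribed, and whether virus was suppressed. A result reported as adherence on any of these would be read as evidence that clients took their treatment, which the field does not show directly.

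This goes beyond a missing definition that could be supplied at analysis. If the fields are not in the extract, no later definition can recover them without going back to the records.

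**Working it through.** No arithmetic applies. The check sets the promised outcome against the fields described.

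**1. Is adherence a separate outcome?** Yes. Sections 1.2 and 2.4 and Appendix B each name it alongside ART initiation and viral suppression, not as a synonym for either.

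**2. Is it defined?** Not in the available text. The closing data analysis plan covers the primary aim only. Table 1 has no adherence row, but the table seems to be cut: it ends in an orphan row, has a footnote marker without a footnote, and also lacks rows for ART initiation and viral suppression. Nothing is inferred from it.

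**3. What can each report field support?**

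| Field in Appendix B | What it supports |
|---|---|
| ART begun; start date | ART initiation |
| Drug names; regimen change; drug change | What was prescribed |
| Viral load tested; result | Viral suppression, among those tested |
| CD4 tested; result; clinical stage | Disease status |
| Age, sex, trust point, HIV confirmation and registration dates | Description and grouping |
| STI testing, diagnosis, treatment; drug clinic registration | Other services |

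No row is a dispensing or refill date, a quantity or days' supply, a missed-dose item, a self-report, or an ART interruption or stop date. Direct adherence variables: 0.

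**4. A test case.** Two clients start the same regimen on the same day. One takes every dose; the other stops. Start status, start date and starting drugs are the same for both. Whether the two change fields differ depends on whether a stop is entered as a change, which the documents do not say. Viral load may differ, but that is the suppression outcome.

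**5. Could AppSheet fill the gap?** Section 3.3 and Appendix A describe it as recording services, tests, programme participation and referrals, with no adherence item named. That list is given as examples, and the questionnaires are attachments outside the documents, so the described count is 0 but the actual count is unknown.

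If an item does exist, two further limits apply:

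- AppSheet covers only clients who consent and hold an ID issued at a BRIDGE trust point.
- Its 6-digit ID links to the anonymous trust point code on a list kept by the trust point nurse. The report's 4-digit ID links to the patient's name on a list kept by AIDS Center staff. No crosswalk is described, so an AppSheet item could not be joined to the report's ART start date.

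**The case against.** **AppSheet is unseen.** AIDS Center nurses complete a survey about services at each visit, and ART dispensing could be one of the items. This stands. A reader might infer that neither source contains an adherence variable. The documents show that for the Semi-Annual Report only. For AppSheet they show that no such item is described and that its stated role under Aim 2 lies elsewhere.

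**Viral load is an indirect marker.** The result sits in the same report row as the ART start date, so suppression among starters could be offered as a sign of adherence. This also stands, and it rules out saying that nothing at all can be learned. But it reuses the laboratory result that already serves the suppression outcome, and only for clients tested in the period. It does not test a second outcome.

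**A stop might be recorded as a regimen change.** Possibly; the documents are silent. Even then, the listed fields do not say how a stop would be told apart from a switch, and they would give no degree of adherence among those who continue.

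**It is one part of a secondary aim.** True. The power statement in Section 2.4 rests on undetectable viral load, and the primary outcomes do not use adherence. This limits the weight of the point but does not remove it.

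**Conclusion.** The point holds in this form: adherence is promised as a separate Aim 2 outcome, the available text does not define it, and the report assigned to it lists no direct measure. From the data described, it cannot be tested as an outcome distinct from viral suppression. The effect is confined to one secondary outcome, in every report period. It should be corrected, but it does not touch the primary conclusions.

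The verdict rests on reading the Appendix B list as complete, which its wording supports, and on the AppSheet description being a fair guide to questionnaires not available here.

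Two further inferences are tempting and should not be drawn:

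- **That ART-ever-started would be used as the proxy and would necessarily favour post-rollout periods.** The plan proposes no proxy. The field does not revert for an individual, but the report covers people served by the AIDS Center, so deaths and transfers can lower the count. Newly diagnosed clients not yet on ART, whom BRIDGE is meant to bring in, can lower the proportion.
- **That a misclassification rate can be stated.** The documents give no rate of stopping ART, so any figure would only return the rate assumed.

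**What to change.** 1. In Appendix B (Indicators Provided in Report), add ART dispensing dates with days' supply and any recorded ART interruption or stop date, if the electronic case system holds them. The documents say only that it holds treatment information, so this must be confirmed first.
2. Pre-specify one adherence measure in Section 2.4, for example the proportion of days covered in the report period, with its threshold chosen by the study team. Apply it identically to pre- and post-rollout periods, and extract earlier periods retrospectively where the records allow.
3. If an AppSheet item already captures this, cite it, define the measure from it, and state which clients it covers.
4. If neither source holds such data, delete ART adherence from Aim 2 in Sections 1.2 and 2.4 and in Appendix B, and make no adherence claim.

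The cost depends on what the case system holds. If the fields exist, it is a few extra columns in a report that AIDS Center staff already prepare every six months, a written definition, and a notice to the ethics bodies. If they do not, it is the removal of one secondary outcome.

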Analysis of Program data: Formal hypothesis testing based on program data will test for differences in outcome measures obtained during the pre-intervention period (i.e., time points before BRIDGE is implemented in a city) versus periods when BRIDGE is implemented. We will employ permutation tests (a.k.a. “randomization tests”) for significance testing because of concerns that the distribution of measures may not be approximated well by a small sample size (i.e.,  $N=24$  TPs). In experimentally controlled trials with small sample sizes, permutation tests have been shown to be superior to parametric tests. As a heuristic and non-parametric approach, permutation testing more accurately estimates the nominal type I error rate for cluster randomized clinical trials with small sample sizes and with measures that may not be normally distributed compared to candidate parametric procedures. Strong hypothesis testing in this manner involves permuting the BRIDGE implementation status of each time point; since the time period “assignment” (pre-implementation vs. BRIDGE) is allocated based on city, permutations will account for clustering by city (i.e., a permutation for TPs in the same city will all be assigned the same implementation status for that time point). Not only does this conservatively account for shared variance that might be present due to being located in the same city, statistical efficiency can be improved by clustered permutation testing. For inference, the test statistic (difference in means) observed based on actual period assignments is compared vis-à-vis the distribution of test statistics using permuted assignments, with the proportion of permuted test statistics greater than the actual observed taken as the one-sided or half of the two-sided p-value. With program measures collected quarterly over 42 months, the number of clustered permutations with 3 study sites (4 cities) is 38,416, allowing testing of statistical significance with  $\alpha < .0001$ . If we permute all 24 TPs independently, tests of significance can be performed with much lower  $\alpha$ . We will conduct both permutation tests with sites permuted independently as well as clustered permutations by city and report the result with the more conservative p-value. Hypothesis testing for Aims 1 and 2—i.e., estimating the effectiveness of the intervention—will involve

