examination of the population-level effect in the statistical models to make inferences about the treatment effect.

Power analyses for Aims 1 and 2: Estimates of power to detect significant differences for each hypothesis was conducted. Power analyses were conducted using G\*Power (v3.1.0), two-tailed hypothesis testing, and  $\alpha=.05$ ; results are presented separately for site level data (Figure 3). For site level data, the smallest effect size for Aims 1 and 2 proportion achieving undetectable viral load; power analyses for this “rate limiting” effect size used unconditional exact test to simulate permutation testing method of estimating p-values as well as simulated cluster permutation (i.e., TPs in a city covary together). The autocorrelation and clustering effects were modeled as overall “intraclass correlation” (ICC), using a range of ICCs observed in our prior studies. Results indicate 80% power is achieved with a sample size of 24 TPs (Figure 4).

[figure not shown]

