### Formal hypothesis testing:

Hypothesis testing draws on data from the Google app-based data collection system. The primary test for these hypotheses will be based on patient visits to NSPs, compared at the site (NSP) level. This test will utilize a repeated measures approach and will examine differences in outcome measures obtained during the time points before Bridge is implemented in a city (pre-implementation) versus time points that follow the initiation of Bridge intervention implementation (implementation) in the city. We will employ permutation tests (a.k.a. “randomization tests”) for significance testing because of concerns that the distribution of measures may not be approximated well by a small sample size (e.g.,  $N = 24$  NSPs). Hypothesis testing in this manner involves permuting the Bridge implementation status of each time point; since the time period “assignment” (pre-implementation vs. Bridge intervention implementation) is allocated based on city, permutations will account for clustering by city (i.e., a permutation for NSPs in the same city will all be assigned the same implementation status for that time point). Not only does this conservatively account for shared variance that might be present due to being located in the same city, statistical efficiency can be improved by clustered permutation testing. For inference, the test statistic (difference in means) observed based on actual period assignments is compared vis-à-vis the distribution of test statistics using permuted assignments, with the proportion of permuted test

statistics greater than the actual observed taken as the one-sided or half of the two-sided p value.

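### The permutation p-value counts only the upper tail and leaves out the observed assignment, so the value labelled two-sided can exceed 1 and cannot flag a decline

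*Combined protocol and SAP*

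**What the plan says.** Section 2.4 (Analysis of Program data) states the aim of the test: it "will test for differences in outcome measures obtained during the pre-intervention period" and the periods under BRIDGE. The statistic carries a sign: "the test statistic (difference in means) observed based on actual period assignments is compared" with the values under permuted assignments, "with the proportion of permuted test statistics greater than the actual observed taken as the one-sided or half of the two-sided p-value".

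The Data Analysis Plan for Primary Study Aim (Formal hypothesis testing) gives the same rule: the share of permuted "statistics greater than the actual observed taken as the one-sided or half of the two-sided p value".

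Neither place mentions equality, ties, the observed assignment, an absolute value or a lower tail. Neither says which of the two p-values will be reported.

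Three further statements bear on the point:

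- Section 2.4 gives the size of the clustered reference set: "the number of clustered permutations with 3 study sites (4 cities) is 38,416". It also plans a second test that permutes the trust points (TPs) independently, and reports the larger of the two p-values.
- The power paragraph of section 2.4 specifies "two-tailed hypothesis testing" at α = .05.
- Section 2.2 randomises the order of three sites over three fixed start months: 22, 28 and 34.

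**The concern.** A two-sided p-value has to respond to extreme results in both directions. Doubling the upper-tail share does so only when the observed statistic lies in the upper half of the distribution. In the lower half the result exceeds 1 and is not a p-value. Testing, linkage or retention could fall during the BRIDGE period, for instance through the funding cuts that section 2.2 names as a possible outside influence. The rule could not flag such a fall, although the plan presents the test as two-sided.

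The second problem is the word greater. The assignment that occurred is one of the possible assignments under the null hypothesis, so a valid permutation p counts it. A strict inequality leaves it out and allows p = 0. How much this matters depends on the size of the reference set.

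**Working it through.** **Inputs.** Signed difference in means and strict upper-tail rule (section 2.4 and the Data Analysis Plan); 38,416 clustered assignments (section 2.4); three sites over three start months (section 2.2); data from month 13 (Appendix A); 24 TPs, 8 per site (section 3.7). The documents give no variance components in the text, so those used below are assumptions.

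**1. The plan's own figure.** "With program measures collected quarterly over 42 months" gives 42/3 = 14 quarters. 14⁴ = 38,416 reproduces the stated count exactly: four cities, each free to start in any of 14 quarters. The three-site version, 14³ = 2,744, does not match. The resolution is 1/38,416 = 0.000026 one-sided and 2/38,416 = 0.000052 two-sided, both below the stated .0001.

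**2. The missing lower tail on the stated set (no ties).**

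| Observed statistic | Share strictly greater | Doubled, as written | 2 × smaller tail, observed included |
|---|---|---|---|
| Largest of 38,416 | 0 | 0 | 2/38,416 = 0.000052 |
| Smallest of 38,416 | 38,415/38,416 = 0.99997 | 1.99995 | 2/38,416 = 0.000052 |

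Equally extreme results in opposite directions get 0 and about 2. The written value exceeds 1 whenever more than half of the permuted statistics exceed the observed one.

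**3. Simulated consequences on the 38,416 set.** The layout was 3 sites × 8 TPs × 14 quarters, with starts after (22 − 13)/3 = 3, (28 − 13)/3 = 5 and (34 − 13)/3 = 7 quarters.

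- True decrease of 0.5 TP-level SD (TP SD 1, residual SD 0.7; 300 trials): the rule as written rejects in 0% and the doubled smaller tail in 38%. The written p exceeds 1 in 99%.
- True increase of 0.5 TP-level SD (300 trials): both rules reject in 30%.
- Separate runs with decreases of 1 and 3 residual SD (site and TP SD 0.5; 300 trials each): the written p exceeds 1 in every trial and is never ≤ .05.
- No effect and no time trend: the written p exceeds 1 in about half of trials (0.478 to 0.502).

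**4. The strict inequality on the stated set.** Counting the observed assignment adds 1/38,416 = 0.000026 to the one-sided p. At two-sided .05 the cut-off is 0.025 × 38,416 = 960.4 assignments, so the rejection region changes by one rank. The written p was 0 in none of 6,000 simulated null trials.

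**5. The strict inequality if the set were the randomised roll-outs.** Three sites over three start months give 3! = 6 orders.

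| Rank, from the top | 1 | 2 | 3 | 4 | 5 | 6 |
|---|---|---|---|---|---|---|
| Doubled, as written | 0 | 0.33 | 0.67 | 1.00 | 1.33 | 1.67 |
| min(1, 2 × smaller tail), observed included | 0.33 | 0.67 | 1 | 1 | 0.67 | 0.33 |

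Under the null each rank has probability 1/6, so the clustered p is 0 in 1 trial in 6. Simulation gave 0.157 to 0.183, consistent with a standard error of √(0.1667 × 0.8333/1,000) = 0.012. The smallest valid values are 1/6 = 0.167 one-sided and 2/6 = 0.333 two-sided.

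**6. With the larger of the two p-values reported, still on six orders.** The TP-level test was taken as 999 random shuffles of start times among the 24 TPs, which is an assumption. The reported p was then 0 in 0% of null trials with no site or TP variation, in 4.2% with site and TP SD both 0.5, and in 17.4% only with a very large site SD of 3. On the 38,416 set it was never 0.

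**The case against.** The best defence is that the plan's hypothesis is directional: the Data Analysis Plan predicts increases only. In that direction the doubled upper tail is the smaller tail doubled, so power and false-positive rate are those of an ordinary two-sided test. A p above 1 would also be noticed. All of this stands, and it limits the damage to the failure to flag a decline. It does not make the formula a two-sided p-value. If a one-sided test is meant, the plan should say so and give its α. At present it leaves open which of two values, differing by a factor of two, will be reported.

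It can also be said that the permutation p is not the only route to inference, because the Data Analysis Plan names mixed models and GEE for hypothesis testing too. That is correct and reduces the weight of this point. The same plan still assigns significance testing to the permutation test, so the rule remains in use.

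A reader might infer that the rule, as planned, declares BRIDGE effective at p = 0 in one null trial in six. The documents do not support this. Section 2.4 fixes the clustered set at 38,416, where the inequality is numerically trivial. It also reports the larger of two p-values, so a clustered p of 0 is not by itself the reported result. The Data Analysis Plan repeats neither the count nor the larger-p rule, but nothing in it proposes a six-order set.

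**Conclusion.** The concern holds in limited form. On any reference set, the rule in section 2.4 and in the Data Analysis Plan has no lower tail, can exceed 1, and cannot give a significant result for a statistic in the lower tail. This contradicts the plan's test for differences and its two-tailed power calculation. It follows from the formula and needs no assumption about variances; only the simulated rejection rates depend on assumed components. It does not bias the test towards benefit.

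Omitting the observed assignment is an error of about 0.00003 one-sided on the stated set. It becomes serious only if the set is first restricted to the six roll-outs that section 2.2 can produce, and it is then softened, by an amount that depends on unknown variances, by reporting the larger p. The formula should be corrected before any such restriction, because restricting the set alone would introduce clustered p-values of 0. Which reference set is appropriate is a separate question that this point does not settle.

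**What to change.** In section 2.4 and in the Data Analysis Plan, replace the p-value sentence with the following rules:

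- One-sided p: the proportion of assignments, observed one included, whose statistic is ≥ the observed value.
- Two-sided p: min(1, 2 × the smaller of the ≥ and ≤ proportions).
- If permutations are sampled: (b + 1)/(B + 1) for each tail, where B is the number sampled and b the number at least as extreme in that tail.
- The two-sided p is the one reported, to agree with the power section.
- The same formula applies to the test that permutes TPs independently.

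The cost is one sentence in each of the two places and one line of code. On the 38,416 set, p-values for increases rise by 0.000026 one-sided or 0.000052 two-sided. If the set is ever limited to the six orders, the corrected clustered test cannot reach .05, and the sponsor should know this before choosing that set.
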